## Abstract

**Background:**

The prevalence of stroke continues to rise in low-middle income countries. The continual rise in stroke cases and increasing prevalence on post-acute needs represent a crucial call for increased accessibility and utilization of rehabilitation services.

**Aim:**

The primary objective of the study is to test the feasibility of a nurse-led telerehabilitation intervention in improving self-efficacy among stroke survivors. The findings of the trial are intended for use in a future larger study.

**Methods:**

Participants would be recruited at the University of Ghana Hospital and randomized into an intervention group and a control group. Participants aged ≥ 18 years, diagnosed of stroke at most 12months prior the recruitment and requiring moderate level of assistance would be considered for eligibility. Participants in the intervention group will receive individualized and comprehensive nurse-led rehabilitation therapies in physical, emotional, cognitive and nursing education domains for 6 months, in addition to treatment as usual (TAU). The control group will only receive treatment as usual. Follow-up evaluations will occur immediately, 30 days and 90 days after the intervention.

**Discussion:**

Providing stroke rehabilitation services in low-resource settings presents a significant challenge due to limited infrastructure and a lack of trained healthcare professionals. The current study has the potential of contributing to the growing body of evidence on the impact of telerehabilitation services in mitigating these challenges in low-resource settings.

## Introduction

In low- and middle-income settings, stroke remains one of the major causes of disability and mortality [1–3]. Patients who suffer a stroke may experience variable degrees of impairment and, in more serious situations, death. The aftermath of a stroke depends on several factors, including patient characteristics, emergency health-seeking behaviour, the nature of the stroke, and post-stroke sequelae [4–6]. It is crucial for stroke survivors with impairments to undergo rehabilitation as part of the recovery process [7].

According to Knect et al. [8], rehabilitation after stroke plays a critical role in improving functional, and cognitive outcomes. Other studies have shown that providing emotional and psychological support for the patient and their caregivers during the rehabilitation process can greatly contribute to overall success [9, 10].

Traditionally, stroke rehabilitation begins after the patient has been physiologically stabilized and is still on hospital admission [11]. This initial rehabilitation phase is primarily focused on improving physical functioning and facilitating the patient’s transition back to their home. This is followed by continuous rehabilitation, which typically takes place between 8 weeks and 6 months after the onset of the stroke. During continuous rehabilitation, patients make practical adjustments in their homes and try to navigate their natural environment with minimal assistance [12].

Despite the enormous impact of rehabilitation on recovery and life adjustment post-stroke, the delivery of equitable and affordable access to rehabilitation remains a challenge globally [13]. This challenge is more prominent in low and middle income countries (LMICs) due to limited rehabilitation infrastructure and inadequate number of trained health workers [14]. In Ghana, access to rehabilitation especially during the continued phase and post-hospital discharge is met with major challenges, including the high cost of available services, limited dedicated stroke rehabilitation services and units, socio-cultural barriers, long waiting times, poor education on rehabilitation and poor communication with healthcare providers [14, 15]. As a result, persons recovering from stroke may have several unmet rehabilitative needs which remains unresolved, and adversely impact the recovery process [14].

These challenges exist partly due to the nature of conventional stroke rehabilitation during the continuous phase. Patients who are undergoing post-discharge rehabilitation mostly have to present themselves at the health facility, receive planned therapy and travel back to their homes [15]. This approach however is wrought with issues such as long travel distances and financial burden which often deter the stoke survivors from returning to use available services inf any. During the COVID-19 pandemic, such travels were virtually impossible in some settings creating a greater need to consider other innovative measures of continuing rehabilitative support even at a distance [16].

Telerehabilitation is becoming a highly considered approach to delivering stroke rehabilitation services. The approach has yielded positive outcomes, including improved stroke self-efficacy, motor functioning, and emotional well-being [17–19]. Telerehabilitation–an emerging means of delivering rehabilitation services remotely using information technology- is projected to be a tremendous solution to the current challenges associated with rehabilitation accessibility. Additionally, a few studies focusing stroke telerehabilitation in Ghana has found the approach to be feasible, acceptable among patients and clinicians and appropriate for addressing challenges such as barriers to physiotherapy [20, 21].

With a limited number of stroke specialists in the country, stroke nurses and community nurses in Ghana have to take a prominent role in supporting stroke rehabilitation [22]. As indicated earlier, the disabling effects of stroke put patients in a critical situation for increased rehabilitation support. Nurses are uniquely placed to support these patients after discharge. According to Kirvevold [12] nurses’ roles in post-discharge stroke rehabilitation includes but are not limited to coordinating treatment and care, providing assistance to survivors and family, providing informational support, consolation, monitoring condition progress, and supporting the resumption of roles and activities. These are all major roles that are crucial for improving patient outcomes and meeting the rehabilitation needs of stroke survivors and caregivers [23]. However, similar to conventional stroke rehabilitation, nurses’ involvement in stroke telerehabilitation is limited, particularly in LMICs [24]. Inadequate specialized nurses, limited policies supporting their role in stroke rehabilitation, and a lack of recognition by other healthcare professionals and caregivers contribute to limitations of nurses’ involvement and practice in stroke rehabilitation [25]. Regardless, post-discharge stroke rehabilitation aligns with the mandate of nursing to promote recovery which places nurses at the core of the process. Despite this assertion, the critical role of nurses in post-discharge stroke rehabilitation especially in LMICs has not been well articulated in existing literature.

It is against this background that an innovative programme of care was developed. The pilot phase of the study seeks to understand the feasibility of a nurse-led telerehabilitation underpinned by the need to support stroke survivors in ADLs performance accomplishments.

### Conceptual framework

The development of the intervention is guided by the self-efficacy model, which posits that an individual’s belief in their ability to perform to achieve certain goals–in this case, activities of daily living–plays a significant role in their motivation and behavioral change [26]. The model suggests that such belief is influenced by a number of sources including mastery experiences, vicarious experiences, social persuasion, and emotional state [27]. In the context of stroke rehabilitations, improving self-efficacy could help stroke survivors better engage in rehabilitation activities and ultimately improve their functional outcomes [28].

The nurse-led telerehabilitation intervention in this study is designed to improve the self-efficacy of stroke survivors by targeting the factors that influence self-efficacy belief. The intervention aims to provide stroke survivors with opportunities for mastery experiences, as well as vicarious experiences through modelling and guidance through achieving daily activities goals. Nursing support would also provide feedback and emotional support to further boost the stroke survivors’ self-efficacy.

The study objective is to assess the feasibility of a nurse-led holistic telerehabilitation among Ghanaian stroke survivors. The primary objectives of the trial are as follows:

Assess the recruitment and retention rates of participants.Assess the user satisfaction of the nurse-led telerehabilitation intervention.Examine the factors influencing user satisfaction of the nurse-led telerehabilitation interventionA secondary objective of the trial is to measure whether a nurse-led telerehabilitation would improve self-efficacy of stroke survivors.

## Methods and analysis

### Study design

The trial is a parallel-group (intervention and control groups) randomized controlled study with 1:1 allocation to assess feasibility of a nurse-led telerehabilitation intervention administered remotely at the homes of Ghanaian stroke survivors. Post intervention process evaluation will employ a mixed method approach to exploring feasibility elements of the intervention.

### Study setting

Study participants would be recruited from the University of Ghana Hospital in Accra, Ghana. The facility has a dedicated stroke outpatient clinic for clients and a physiotherapy unit. We have already engaged with the chief nurse officer, lead physiotherapist, and head of the stroke clinic of the hospital, who are key to the success of the participant recruitment process.

### Eligibility criteria

Study participants will be considered for inclusion if they meet the following criteria:(1) is 18 years or above (2) diagnosed of a stroke with an onset of 1 week to 12 months prior the intervention (3) has FIM score of 55–100 (Level 3 moderate assistance) (4) total NIHSS score of 5–15 (moderate stroke). However, study participants would be excluded subject to these criteria: (1) has no access to a smartphone and standard internet connectivity (1.0 mgbs) (2) is unavailable for follow-up interviews (3) has a cognitive impairment (as documented in the patient’s medical records) that makes it difficult to comprehend the information provided and limits capacity to provide consent.

### Recruitment and screening

Participants would be recruited from the medical department and the stroke clinic of the University of Ghana Hospital. Patients at the study setting would be approached onsite by recruitment nurses who are independent from the study investigators and provided comprehensive background information about the study, including its risks and benefits during first encounter as part of inviting them to consider participating. If they opt to participate, eligibility clinical screening based on aforementioned criteria will be completed by the recruiting nurse.

In this regard, the nurse will complete the FIM and NIHSS scores to ascertain eligibility. Informed consent would be obtained by researchers at this point (S1 Fig). This informed consent has been approved by the Noguchi Institutional Review Board 032/21-22.

### Randomization, allocation and blinding

After eligible participants have provided informed consent and undergone baseline screening, they would be randomly assigned to the intervention group (Nurse-led rehabilitation support + Treatment as usual) and control group (only treatment as usual).

Randomization would be conducted by an independent researcher who is not involved in the study. She will use a combination of block and stratified randomization to assign 40 participants to either the intervention group or the control group. Prior to the assignment, participants would be stratified based on the type of stroke (hemorrhagic vs ischemic). Within each stratum, participants will be assigned using block randomization with block size of four. Additionally, the independent researcher would generate random sequence for the block order with an online random sequence generator (sealedenvelope.com). The sequence numbers would be written and placed in opaque envelopes by the independent researcher. Immediately a participant signs the consent form, the principal investigator ([name]) would inform to sequentially open the envelope in the corresponding block and assign participant to the group indicated in the envelope.

Participants will not be blinded to the assigned group. Also, It will not be possible to blind the interventionists (stroke nurses and other health professionals) providing the intervention in this study. Essentially both parties (participants and interventionists would be unmasked. However, the assessors of study outcomes would be blinded to the allocation of participants. Also, assessors gathering baseline data on self-efficacy and any other data after group allocation would be blinded to the allocation status of participants.

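### A fixed, published block size of four lets anyone who tracks allocations by stratum know about 30–33% of them in advance in this unmasked, single-hospital trial

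*Protocol article*

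**What the plan says.** The Study design section describes a "randomized controlled study with 1:1 allocation". Study setting names a single source of participants: "Study participants would be recruited from the University of Ghana Hospital in Accra, Ghana".

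The section Randomization, allocation and blinding gives the procedure. An independent researcher generates the sequence: "She will use a combination of block and stratified randomization to assign 40 participants to either the intervention group or the control group". Beforehand, "participants would be stratified based on the type of stroke (hemorrhagic vs ischemic"), and then: "Within each stratum, participants will be assigned using block randomization with block size of four". The allocations go into opaque envelopes prepared by that researcher. Once consent is signed, the principal investigator "would inform to sequentially open the envelope in the corresponding block and assign participant to the group indicated in the envelope". The object of the verb is missing, so the text does not say who opens the envelope. On masking: "Essentially both parties (participants and interventionists would be unmasked". Outcome assessors are blinded.

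Under Recruitment and screening, nurses independent of the investigators approach and screen patients, and researchers obtain informed consent. The article describes no variation of the block size and no step to withhold it from the investigators.

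**The concern.** With a known block size and 1:1 allocation, once one arm has filled its two places in a block the rest of that block is settled. In an open trial at one hospital, past allocations can be seen by the people running it, and the block size is in print. A person who knows a candidate's stroke type and the allocations so far in that stratum can sometimes know the next allocation before consent is taken. An opaque envelope hides its contents; it cannot hide what the block structure implies.

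That foreknowledge could influence when, or whether, consent is sought from a particular patient. The comparison most exposed is the group comparison of the Stroke Self-Efficacy Questionnaire (SSEQ), because it is the only between-group test in the Data analysis section. The make-up of the intervention arm is also exposed. With 20 planned per arm, one steered participant is 1/20 = 5% of an arm.

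**Working it through.** **Inputs from the article.** Block size 4; 1:1 allocation, so two places per arm in each block; 40 participants; two strata, with the split not given. The article states no predictability figure, so there is none to reproduce.

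**Assumptions.** The observer knows the block size and all earlier allocations in the stratum, and knows the stroke type of the next candidate.

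**Step 1: certain allocations in a complete block.** The six equally likely blocks are AABB, ABAB, ABBA, BAAB, BABA and BBAA. An allocation is certain once one arm has its two places.

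- Places 1 and 2: never certain.
- Place 3: certain when the first two match (AABB, BBAA), probability 2/6 = 1/3.
- Place 4: always certain.

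Expected certain places per block = 1/3 + 1 = 4/3. Share = (4/3)/4 = 1/3 = 33.3%. By direct count: (2 × 2 + 4 × 1)/24 = 8/24.

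**Step 2: all 40, allowing for unfilled last blocks.** A last block that stops after 1, 2 or 3 places contributes 0, 0 or 1/3 certain allocations.

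| Stratum sizes | Certain allocations | Share of 40 |
|---|---|---|
| Both multiples of 4 | 10 × 4/3 = 13.3 | 33.3% |
| Remainders 1 and 3 | 9 × 4/3 + 1/3 = 12.3 | 30.8% |
| Remainders 2 and 2 | 9 × 4/3 = 12.0 | 30.0% |

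These cases cover every possible split of 40 into two strata.

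**Step 3: best guess.** Guess the arm that is behind, and toss a coin when the arms are level. The chance of being right by place is 1/2, 2/3, (1/3 × 1 + 2/3 × 1/2) = 2/3, and 1. The mean is (1/2 + 2/3 + 2/3 + 1)/4 = 17/24 = 70.8%, against 50% under simple randomization.

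**Step 4: alternatives.** Fixed sizes are by enumeration. Varied sizes are by simulation: 4,000 runs of one sequence of 40, with an observer who knows the set of sizes and all past allocations but not the current size.

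| Block sizes | Certain | Best guess right |
|---|---|---|
| Fixed 4 | 33.3% | 70.8% |
| Fixed 6 | 25% | 68.3% |
| Random 2, 4 | 10.8% | 72.0% |
| Random 4, 6 | 5.6% | 68.9% |
| Random 2, 4, 6 | 4.1% | 70.1% |
| Random 4, 6, 8 | 2.3% | 67.6% |

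Varying the size removes most of the certainty (4.1% of 40 is 1.6 allocations). It hardly changes the best-guess rate.

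**The case against.** Several safeguards are already planned. Sequence generation is independent, envelopes are opaque and opened in order, assignment follows consent and baseline screening, outcome assessors are blinded, and independent nurses decide who is approached and screened. Nothing says those nurses see past allocations. Small blocks also have a purpose here: with 40 participants in two strata of unknown size, they limit imbalance.

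These points narrow the opportunity. They do not close it, because researchers take consent, may know past allocations, and the block size is stated. Blinded assessment protects measurement, whereas selection acts before enrolment.

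Four stronger readings are tempting, and the article does not support them:

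- **That the principal investigator opens the envelopes.** The sentence is incomplete. Since the same section says an independent researcher conducts the randomization, it may equally mean that the investigator notifies that researcher, who opens the envelope.
- **That one in three allocations is predictable in any circumstances.** The figure needs someone tracking allocations by stratum, and 33.3% needs complete blocks.
- **That the primary outcomes are shown to be biased.** Satisfaction concerns delivery of the intervention, and the data collection section appears to place it in the intervention arm only. No between-arm test of retention is stated. Steering could alter who is in the intervention arm and so shift these rates, but the size of any such shift has not been shown.
- **That varied blocks would cure the 71% best-guess rate.** They leave it at about 68–72%.

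**Conclusion.** The concern holds as a risk created by a rule that the article states, with an inexpensive improvement available. About 30–33% of allocations, 12 to 13 of 40, could be known with certainty in advance. This rests on an observer who knows the block size, the past allocations in the stratum and the next candidate's stroke type; the range reflects the unstated stratum split. It is an expected ceiling on certain foreknowledge and does not show that anyone would act on it. The main exposure is the secondary SSEQ comparison, which the Limitations section already treats as possibly too small to detect differences, together with the composition of the intervention arm. Who opens the envelope cannot be settled from the text and needs correction in its own right.

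**What to change.** 1. Have the independent researcher generate the list in each stratum with randomly varying block sizes, for example 2, 4 and 6. Keep the sizes from recruiters and from those taking consent. File the envelopes as one continuous run per stratum with no sign of where a block ends: the present wording refers to the corresponding block, which may suggest that they are grouped by block.
2. Rewrite the unclear sentence so that the independent researcher, on notice from the principal investigator, opens or releases each allocation after consent and baseline screening are complete.

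Assignment after consent and opaque envelopes opened in sequence are already planned and need no change.

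**Cost.** A new list and an edited sentence. If enrolment has begun, the change can apply to blocks not yet started. An unfinished block of six can leave an imbalance of three in a stratum instead of two; over both strata the worst case rises from 2 × 2 = 4 to 2 × 3 = 6. What is gained is the loss of most certain predictions and a clear separation of release from the study team; the best-guess rate will stay near 70%.

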#### Initial and ongoing patient assessment

Participants would undergo various assessments on motor function, cognitive capacity, anxiety and depressive levels and nutritional status utilizing evidenced-based assessment tools. The initial assessment would span in the first week of the intervention. Based on the problems and needs identified during the assessment, participants would receive a bundle of interventions in the domains of cognitive rehabilitation, physical rehabilitation, emotional support, and stroke education. These interventions would be provided twice a week in 1hr-to-1hr 30mins per session via video calls on WhatsApp or phone calls. These calls would be scheduled weekly with the participants after needs and availability assessment to improve response. Participants with close-by caregivers would be asked to provide the contacts of their caregivers as back-up. A participant in the intervention may have 192 sessions maximum or 48 sessions minimum in the span of the intervention.

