### Data collection, entry and management

Data would be gathered from participants before the intervention but after recruitment and after the intervention. Baseline data would be gathered on two occasions prior to the intervention. Before randomization, data on participant demographic characteristics, patient history, functional status, psychological functioning and cognitive capacity would be gathered. Baseline data on patient’s self-efficacy would be collected before the first session of the intervention via phone survey. The second phase of data collection would take place immediately after the end intervention capturing quantitative date on user satisfaction, qualitative data on experiences throughout the intervention only for participants in the intervention group and stroke-self efficacy levels for participants in both group. The third and final phase of data collection would be executed 4 weeks and 12 weeks after the intervention respectively capturing stroke efficacy levels in both groups. The data collection process would be undertaken by an independent assessor who are unaware of participant allocation. After completing each phase of data collection, the quantitative data would be entered into a spreadsheet using Microsoft Excel. The data would be processed for outliers and missing inputs. Qualitative interviews would be audiotaped, audios would be saved in a PC folder and later transcribed for analysis. The entered information and saved audios would be protected by a password only accessible by the research team.

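### Baseline self-efficacy (SSEQ) is collected after allocation from unblinded participants, so the change-over-time analysis and the baseline comparison of arms can carry an allocation effect; the stated order of randomisation also needs reconciling

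*Protocol article*

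**What the plan says.** All references are to the protocol article.

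- **Two baseline occasions.** Data collection, entry and management describes the first as: "Before randomization, data on participant demographic characteristics, patient history, functional status, psychological functioning and cognitive capacity would be gathered". Self-efficacy is not on that list. It is handled separately: "self-efficacy would be collected before the first session of the intervention via phone survey".
- **Position relative to allocation.** Randomization, allocation and blinding states that "assessors gathering baseline data on self-efficacy and any other data after group allocation would be blinded to the allocation status of participants". The same section says that participants are not masked.
- **Timing of randomisation.** That section first says: "After eligible participants have provided informed consent and undergone baseline screening, they would be randomly assigned". It then ties the opening of the envelope to a different moment, "Immediately a participant signs the consent form", at which point the step is to "sequentially open the envelope in the corresponding block and assign participant to the group indicated in the envelope".
- **Status of the SSEQ.** Secondary outcome names it as the clinical outcome and describes a 13-item questionnaire on the survivor's ability and confidence.
- **Analysis.** Data analysis plans a Mann-Whitney test (or parametric equivalent) between groups at each follow-up, and a Friedman test (or parametric equivalent) for change over time, both at two-sided 0.05.

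**The concern.** A baseline should be fixed before anything that depends on the assigned group can influence it. Here the respondent is unmasked and the instrument asks how confident the respondent feels. Someone who has just learned that six months of nurse support will, or will not, follow may answer differently. Masking the interviewer protects against interviewer bias but not against the respondent's own knowledge.

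If that happens, baseline SSEQ differs between arms for a reason other than chance. Change measured from it mixes the reaction to allocation with real change, and the baseline table no longer shows whether randomisation balanced the arms on this variable. Later analysis cannot repair this, because no uncontaminated value exists. The results are meant to inform a larger study, so the distortion could be carried forward.

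The conflicting accounts of envelope opening add to the problem. If the envelope is opened at the moment of consent, other baseline data intended to precede randomisation may also fall after it.

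**Working it through.** **1. Is the baseline SSEQ after allocation?** The sentence on assessor blinding could be parsed so that the phrase about allocation applies only to the other data. Three things count against that parse. The word *other* puts baseline self-efficacy among the data gathered after allocation. Masking an assessor to allocation has no purpose before allocation exists. And the data-collection section leaves self-efficacy off its pre-randomisation list, placing it in a separate phone contact before the first session. The two sections agree.

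**2. Does the participant know the group by then?** No sentence gives the moment of disclosure. Assignment is made when the envelope is opened, and participants are not masked. Knowledge before the phone survey is therefore probable, and nothing in the text prevents it.

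**3. Which analyses use the baseline?**

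| Analysis | Uses baseline SSEQ? | Exposed? |
|---|---|---|
| Mann-Whitney between groups at each follow-up (planned) | No | No |
| Friedman test of change over time (planned) | Not stated; natural reading is yes | Yes, if so |
| Baseline comparison of arms | Yes | Yes |
| Change-score or baseline-adjusted comparison (not planned) | Yes | Yes, if later done |
| Feasibility and satisfaction (primary) | No | No |

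**4. How large could it be?** The article gives no figure to reproduce, so this is an illustration.

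- From the article (Proposed sample size): 20 per group and 20% attrition, so 20 × 0.8 = 16 completers per arm.
- Assumed: a baseline shift d of 0, 0.2, 0.3 or 0.5 SD in one arm; correlation r between visits of 0.5 or 0.7; normal data; four time points (baseline and three follow-ups); no true effect; Friedman test applied within the shifted arm. There were 3,000 simulated trials per setting.

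Percentage of trials significant at 0.05:

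| r | d (SD) | Mann-Whitney, first follow-up | Friedman, shifted arm | Mann-Whitney on change (not planned) |
|---|---|---|---|---|
| 0.5 | 0 | 4.1 | 4.5 | 4.9 |
| 0.5 | 0.2 | 3.8 | 9.2 | 7.2 |
| 0.5 | 0.3 | 4.9 | 14.4 | 12.4 |
| 0.5 | 0.5 | 4.7 | 36.7 | 25.4 |
| 0.7 | 0 | 4.7 | 4.4 | 4.5 |
| 0.7 | 0.2 | 5.0 | 11.3 | 10.5 |
| 0.7 | 0.3 | 4.8 | 21.3 | 16.4 |
| 0.7 | 0.5 | 5.7 | 57.6 | 40.0 |

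The follow-up comparison stays at about 4–6% whatever the shift. The Friedman test within the shifted arm does not.

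For the unplanned estimates the bias follows directly: d for a change score (0.2 to 0.5 SD), and r × d after baseline adjustment (0.5 × 0.2 = 0.10 SD to 0.7 × 0.5 = 0.35 SD).

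**5. Order of randomisation.** Recruitment and screening has the nurse complete FIM and NIHSS before consent is taken, so those scores can exist when the envelope is opened. The psychological and cognitive data cannot be placed so easily. If the envelope is opened at signature, they must be collected either before consent or after allocation. The first contradicts the statement that baseline screening comes between consent and assignment, if that screening includes them; the second contradicts the data-collection section.

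**The case against.** The strongest reply is that the comparison that matters is unharmed. The planned between-group test uses follow-up values only, and the simulation confirms that its error rate does not move. A reader might infer that the trial's estimate of effect on self-efficacy is biased. The documents do not support that, because neither a change-score nor a baseline-adjusted comparison is planned. This part of the reply stands in full.

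It can also be said that the Friedman test compares time points, not arms, so it estimates no treatment effect. In people within 12 months of a stroke, recovery alone can make it significant. That is fair and limits what the test could show in any case. It remains one of the two stated SSEQ analyses, and a contaminated starting value adds an avoidable source of error.

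Other limits also stand:

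- The shift has no source in the documents, and its direction cannot be predicted.
- It is tempting to say that participants have been told their group before the survey. The article does not say so; it is a probable inference.
- It is tempting to say that opening the envelope at consent leaves no room for any pre-randomisation data. That goes too far, because FIM and NIHSS can come first.
- The assessment described by "The initial assessment would span in the first week of the intervention" might be read as a further late trial baseline for self-efficacy. The SSEQ is not among the measures listed there, so it does not bear on this point.
- The SSEQ is secondary, and Limitations already concedes that the sample may be too small to detect group differences.

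**Conclusion.** The point holds in a limited form. Two sections place the baseline SSEQ after allocation, in unmasked participants, on a self-reported confidence scale, with a safeguard that acts on the wrong person. Exposed are the change-over-time analysis (if it includes baseline), the baseline comparability of the arms, and any later analysis that uses the baseline. The follow-up comparison between arms and the primary feasibility outcomes are not exposed by this route.

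The size cannot be known from the documents. The range of roughly 9% to 58% for false-positive Friedman results rests on assumed shifts of 0.2 to 0.5 SD, correlations of 0.5 to 0.7, and a test run within the shifted arm. It shows that modest shifts would matter for that test, not that they will occur.

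The conflict over when the envelope is opened is a separate inconsistency in the text and needs no assumption about effect size. Both matters deserve correction before enrolment, because a baseline taken too late cannot be recovered. In a feasibility trial the weight is moderate.

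**What to change.** 1. In Data collection, entry and management, move the baseline SSEQ to the pre-randomisation occasion in both arms. It can remain a phone survey by the same assessor if that is preferred. This also gives both arms one common reference point in place of the first intervention session, which controls do not have.
2. In Randomization, allocation and blinding, replace the clause that opens the envelope at signature with: *The envelope is opened only after consent, eligibility (FIM and NIHSS) and all baseline data, including the SSEQ, have been recorded.* Amend the assessor-blinding sentence so that it no longer places baseline self-efficacy after allocation, and reconcile this section with the data-collection section.
3. In Data analysis, state whether the change-over-time test includes baseline.

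Cost: one questionnaire is given earlier, there is a short delay between consent and allocation, and the IRB and registry must be notified, as Ethics and dissemination requires for modifications. The sample size does not change. With no allocation-induced shift (d = 0), all three simulated tests run at about 4–5%.
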